### Outcomes

All outcome measures and data collection timepoints are listed in Table 3. A differentiation is made between parental and child questionnaires. Fatigue severity, impact of fatigue on daily life and school presence will be measured weekly. All questionnaires will be administered in Dutch.

**Table 3 Tab3:** Time points of all questionnaires and other measurement instruments

	Measurements	T0	T1	Weekly	Intervention
**Main outcome measures**					
Fatigue severity	CIS, subscale fatigue severity	C	C	C	
	PedsQL-MFS	C, P	C, P		
**Secondary outcome measures**					
Quality of life	CHQ	C, P	C, P		
School attendance	School attendance questionnaire	C, P	C, P	P	
Physical functioning	CHQ, subscale physical functioning	C, P	C, P		
	PedsQL-MFS, subscale physical functioning	C	C		
Impact on daily life	Two weekly items (see the ‘Methods/design’ section)			C	
Self-rated improvement	Self-rated improvement questionnaire	C	C		
**Indicators for treatment goals and therapeutic guidance**					
Sleep problems	Sleep diary				C
Level of activity	Activity diary				C
Dysfunctional cognitions about the disease and fatigue	ICQ	C			
	Self-efficacy Scale	C			
Mental fatigue	CIS, subscale concentration	C	C		
Parenting stress	PIP	P			
**Other measures**					
Demographic variables	Age, gender, education, physical problems, and comorbidities	P			
Disease- and treatment related variables (medical record)	Diagnosis, genetic mutation, affected family members, current/past treatments, time since diagnosis				
Feasibility	Questions regarding patient eligibility, response rate, willingness to participate, commitment and satisfaction with the intervention.		C, P, T		
Evaluation/Feedback	A process evaluation focused on treatment integrity, feedback of the therapist and patient on: the intervention, use of the website, and blended nature of the intervention		C, P, T		

Note: *T0*, baseline assessment; *T1*, post-intervention assessment; *weekly*, weekly measurements throughout the entire study; *C*, child questionnaire; *P*, parent questionnaire; *T*, therapist questionnaire

#### Primary outcomes

Fatigue severity will be measured weekly using the Checklist Individual Strength (CIS) subscale fatigue severity (8-items, 7-point Likert Scale), the primary outcome measure [40, 41]. Scores range from 8 to 56; a higher score indicates a higher level of fatigue. A score of 35 or higher is an indication of severe fatigue.

In addition, fatigue severity will be measured at baseline and post-intervention assessment with the Pediatric Quality of Life Inventory Multidimensional Fatigue Scale (PedsQL-MFS) [42], and the CIS subscales ‘fatigue severity’ and ‘concentration’. Both the CIS and PedsQL-MFS have demonstrated sufficient validity, with Cronbach’s alpha’s of 0.90 and at least 0.70, respectively [40, 43].

#### Secondary outcomes

Quality of life will be measured with short forms of the Child Health Questionnaire (CHQ). The CHQ-SF for children consists of 45 items divided in 14 physical and social domains and two overall scales: physical health and psychosocial health [44]. The CHQ-CF45 is valid and reliable with a median Cronbach’s alpha of 0.89 [45]. The parent form (CHQ-PF28) is also valid; the summary measures show adequate reliability with Cronbach’s alpha larger than 0.70 [46]. Impact on daily life is also measured weekly with two items: The patient answers whether the fatigue has interfered with their activities during the week and if it did, how much distress it caused. Both items are answered on a 5-point Likert scale.

School attendance (work/internship) will be expressed in (attended hours/obliged hours × 100). Parents will answer weekly questions regarding school (work/internship) presence: how often and how long their child was not present at school, and the reasons for the absence.

Physical functioning will be measured by the subscale physical functioning of both the CHQ and PedsQL Multidimensional Fatigue Scale.

Self-rated improvement is measured by one item on which patients indicate whether they feel much better, have the same complaints or have become worse compared with the previous measurement at T0. An additional open-ended item will ask whether they consider the intervention helpful in dealing with their fatigue and if they notice a difference in daily life [26].

#### Other study parameters

Demographic characteristics will be determined during baseline assessment (T0). Disease- and treatment-related variables will be collected from the patients’ medical record via the participants’ physician.

Furthermore, the intervention will be evaluated in terms of feasibility by looking at patient eligibility, response rate, willingness to participate, commitment and satisfaction with the intervention. A process evaluation will focus on treatment integrity and feedback of the therapist and patient on the intervention, use of the website and blended nature of the intervention.

Additional instruments to assess which modules and assignments of the PowerMe intervention are indicated will be filled out during baseline assessment (T0) and consists of the following questionnaires: Illness Cognitions Questionnaire (ICQ) [47] and Self-Efficacy Scale [48, 49]. Parents will fill out a questionnaire on parenting stress related to caring for a child with a medical condition (Pediatric Inventory for Parents) [50].

### Power

The sample size and series length are based on literature of randomization tests in multiple baseline single case experiments. Power of a multiple baseline single case experiment is related to the series length [31, 33, 34]. A series length of 30 has a power over 0.8 when the effect size is 1.0 and no autocorrelation is present [33], though some autocorrelation can be expected and will be taken into account. Sample size is based on the primary outcome of fatigue severity using at least 30 weekly measurements. When using randomization tests, a sample size of at least 4 participants per group is necessary to have sufficient statistical power in the randomization test [33, 51]. Based on the literature, the current design of five patients and 33 measurements will be sufficient to reach a statistical significance *p* < .01 using the Wampold-Worsham procedure [33], with significance reached at *p* < .05.

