### Recruitment and study population

Five patients between 8 and 12 years old and five patients between 12 and 18 years old will be included. Specialized metabolic physicians and nurses working at the Radboud Center for Mitochondrial Medicine at the Radboud university medical center in the Netherlands will recruit children diagnosed with MD. Patients will be informed about the PowerMe study during regular medical follow-up, or by an information letter. Furthermore, advertisements will be placed online by the patient organization International Mito Patients (IMP) and the Dutch Foundation for Muscular Diseases (‘Prinses Beatrix Spierfonds’). All interested patients will be screened for eligibility with online questionnaires. Inclusion and exclusion criteria are shown in Table 1. Patients and their parents will sign informed consent forms before filling out the questionnaires. Patients who meet the criteria for a possible anxiety or depressive disorder will be interviewed by a psychologist to make an appropriate assessment of the eligibility of the patient for the study or whether a referral to regular care is advised. Subsequently, the researcher will contact the patient and parents with the results of the screening. If the patient is eligible for the study, the researcher will give a more detailed explanation about the study and answers all questions of the family. Informed consent will then be signed.

**Table 1 Tab1:** Inclusion and exclusion criteria

Inclusion criteria	Exclusion criteria
- Age between 8 and 18 years - Able to speak, write, and read Dutch - Diagnosed with mitochondrial disease (genetically confirmed) - Being severely fatigued (CIS fatigue severity ≥35) - Access to a computer with internet connection - Basic computer skills - Able to travel to the hospital for the CBT intervention (3 sessions)	- Intellectual disability (developmental age younger than 8 years). - Primary depression (CDI ≥16) or anxiety disorder (SCARED-C ≥ 25) - Current psychological treatment for fatigue

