### Procedure

To ensure sufficient data points are present to analyse the data, this multiple baseline single case experiment consists of 33 weekly measures of fatigue dispersed over three consecutive phases: baseline, treatment and follow-up. The intervention will be introduced staggered across time. In other words, each participant will start after a different length of the baseline period. The participants are allocated to an intervention start point at random. The following five start points will be randomized: the therapy will start following a baseline period of 5, 6, 7, 8 or 9 weeks. This approach is similar in both groups. The baseline period should be stable. Five to nine data points should give a clear indication of the stability of the baseline [28, 30]. However, extending the baseline period when an unstable baseline is present will cancel out the randomization. For a more rigorous method of testing the effect of the intervention, baseline randomization will be applied. Therefore, baseline stability will not be checked before starting the intervention.

The researcher will contact the patient after randomization has allocated a baseline period between 5 and 9 weeks. At the start of the study, a participant number will be assigned to the patient to ensure confidentiality of personal identifiable patient data throughout the entire study. Participants and their parents receive a link to the online questionnaires each week for 33 weeks: the children fill out assessments about their fatigue and parents report on the school presence of their child. At the start of the study, the patient and parents are asked to fill out additional online questionnaires for the baseline assessment (T0).

After 5–9 weeks, the patient will start with the PowerMe treatment. The guideline for the treatment duration is 16 weeks. However, it can range from 12 to 20 weeks, tailored to the needs of each participant. Afterwards, the patient fills out the (online) post-intervention questionnaires (T1) and continues with the weekly questionnaire for 8–12 weeks. In Fig. 2, an overview of the study design is shown.

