### Intended statistical analyses

The primary objective of the PowerMe study is to examine the efficacy of the blended CBT on reducing fatigue severity in children with MD. The weekly measurements will be analysed with (1) visual analysis, (2) randomization tests and (3) multilevel modelling.
Visual analysis will be used for an initial assessment of the intervention effects on fatigue severity by examining six features of graphed SCE data: level, variability, trend, immediacy of effect, overlap and consistency of data patterns [52]. On a group level, heterogeneity between individual trajectories will be explored and described.Randomization tests will be used to test if there is a statistical significant effect of CBT on fatigue. These tests have the ability to detect smaller changes than visual analysis alone and test statistical significance. We expect the fatigue severity to be lower in the treatment phase than in the baseline phase. Therefore, we will use a one-tailed alternative hypothesis, measuring the difference in fatigue severity between phases A and B [34, 51].Multilevel modelling will be used to investigate statistical significance and treatment effects using a multiple, single case multilevel modelling strategy based on the modelling suggestions by Moeyaert et al. (2014). This approach can identify case-specific treatment effects and estimated differences between cases. The fluctuations of the weekly and/or aggregated scores between the phases (baseline, intervention and follow-up) are evaluated. More specifically, the analysis focuses on the differences in the intercept and slopes of the weekly scores from one phase to the other. This method has also been validated in small sample sizes (with *N* of 4–8) [53].

All other outcomes will be mapped descriptively. The software program RadQuest will be used to administer questionnaires, which will prevent missing data within questionnaires. According to the study design, missing measurement moments will be handled as missing data and will not be imputated. Analyses of the data will follow the intention-to-treat principle, using the SCDA plug-in package for R software [35, 54].

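### The Power section's figure above 0.8 at effect size 1.0 does not fit start points one week apart (about 0.48 per group of five), and p < .01 is the smallest attainable p-value, not power

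*Protocol article*

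**What the plan says.** The Power section links power to series length and gives one literature figure: "A series length of 30 has a power over 0.8 when the effect size is 1.0 and no autocorrelation is present". It adds that some autocorrelation is to be expected, without giving a size, and that at least four participants per group are needed for adequate power. It then concludes that "the current design of five patients and 33 measurements will be sufficient to reach a statistical significance" at p < .01 "using the Wampold-Worsham procedure", "with significance reached at *p* < .05".

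The design to which this is applied is set out elsewhere. Under Recruitment and study population: "Five patients between 8 and 12 years old and five patients between 12 and 18 years old will be included". Under Procedure: "the therapy will start following a baseline period of 5, 6, 7, 8 or 9 weeks", and "This approach is similar in both groups". Under Intended statistical analyses, for the randomization test: "we will use a one-tailed alternative hypothesis, measuring the difference in fatigue severity between phases A and B". The Background expects a delayed effect, in most cases after 8 weeks.

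The Power section does not mention the spacing of the start points.

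**The concern.** The Wampold-Worsham procedure compares the observed allocation of five start points to five patients with all 5! = 120 possible allocations. The test can succeed only if a wrong allocation gives a visibly smaller phase difference than the true one. With start points from 5 to 9 weeks, a wrong allocation relabels at most 9 − 5 = 4 of a patient's 33 weeks, so the 120 arrangements resemble one another closely. Series length alone cannot make up for that, and a power figure tied to series length need not carry over.

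The p < .01 claim and the four-participant minimum both coincide with the resolution of the test: 1/5! and 1/4!. Resolution says which p-values are possible. It does not say how likely they are.

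This paragraph is the sample-size justification. A reader who relies on it would take a non-significant randomization test in a group of five as the result of a test with more than 80% power. If the true figure is near one half, that reading is wrong, and in a rare paediatric disease the study is unlikely to be repeated soon.

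**Working it through.** **Inputs from the protocol article**
- Five patients per group, 33 weekly measurements; cited power above 0.8 at effect size 1.0, series length 30, no autocorrelation; Wampold-Worsham procedure; significance level 0.05 (Power).
- Start after 5, 6, 7, 8 or 9 baseline weeks; treatment phase of 16 weeks, range 12 to 20 (Procedure).
- One-tailed comparison of phases A and B (Intended statistical analyses).
- Delay of about 8 weeks (Background).

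**Assumptions, not in the article:** normal errors, effect size in within-phase standard deviations, a mean-difference statistic, and autocorrelation values of 0.1, 0.3 and 0.5.

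**Step 1: the p-value claims**
- Five patients: 1/5! = 1/120 = 0.0083. This matches p < .01.
- Four patients: 1/4! = 1/24 = 0.042. This is below 0.05, so it matches the four-participant minimum.

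**Step 2: the test**
- Statistic: the sum over the five patients of (mean of A − mean of B).
- p = (number of the 120 allocations with a statistic at least as large as the observed one) / 120.
- Reject if p ≤ 0.05, that is, if the observed allocation ranks in the top 6 of 120. This is slightly more generous to the plan than a strict p < .05.
- 20,000 simulated trials for the main results. Rejection under no effect was 0.047 to 0.051, so the simulation is calibrated.

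**Step 3: the cited figure**

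Effect size 1.0, five patients, 30 measurements, no autocorrelation, immediate effect, first start after 5 weeks:

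| Spacing of start points | Power |
|---|---|
| 1 week (5, 6, 7, 8, 9) | 0.49 |
| 2 weeks (5, 7, 9, 11, 13) | 0.70 |
| 3 weeks (5, 8, 11, 14, 17) | 0.82 |
| 4 weeks (5, 9, 13, 17, 21) | 0.88 |
| 5 weeks (5, 10, 15, 20, 25) | 0.90 |

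Power above 0.8 is therefore attainable at this series length and effect size, but only with a spacing of about three weeks or more. The protocol's one-week spacing does not reproduce it.

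**Step 4: the protocol's own design**

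Start points 5 to 9, five patients, 33 measurements:

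| Setting | Power |
|---|---|
| Effect 1.0, B = 16 weeks | 0.48 |
| Effect 1.0, B = 12 weeks | 0.47 |
| Effect 1.0, B = 20 weeks | 0.48 |
| Effect 1.0, all later weeks as B | 0.49 |
| Effect 1.0, autocorrelation 0.1 | 0.45 |
| Effect 1.0, autocorrelation 0.3 | 0.42 to 0.44 |
| Effect 1.0, autocorrelation 0.5 | 0.41 to 0.43 |
| Effect 1.5, no autocorrelation, B = 16 weeks | 0.77 |
| Effect 2.0, no autocorrelation, B = 16 weeks | 0.93 |

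Power of 0.80 is reached at an effect of about 1.6 without autocorrelation, and about 1.7 to 1.75 at autocorrelation 0.3. If start points were drawn independently for each patient rather than permuted, power would be 0.46 to 0.48. The chance of obtaining p < .01 at effect size 1.0 is about 0.15 to 0.17.

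**Step 5: the hypothesised 8-week delay**

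Effect size 1.0, no autocorrelation:
- Unshifted A versus B: about 0.05, the level of the test.
- Phase boundary moved by exactly 8 weeks: about 0.44 to 0.53, depending on how much follow-up counts as B.
- A kept as baseline, with B counted only from week 8 of a 16-week treatment phase: about 0.26.

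**Step 6: both age groups pooled**

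A stratified test of all ten patients, with effect size 1.0, an immediate effect and no autocorrelation, gives about 0.78.

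**The case against.** Several points on the other side have weight.

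- **The figure above 0.8 is a citation, not a calculation for this trial.** This is true, and the start points used in the cited source cannot be seen from the article. The spacing comparison shows that spacing matters, not what the source did. But the section uses the figure to support this design, and for this design it does not hold.
- **Being sufficient to reach p < .01 is literally correct.** A p-value of 0.0083 is attainable, and a minimum of four patients is a valid necessary condition, since three give 1/3! = 0.167. What stands against this is the use made of it: attainability is offered as the sample-size justification, and the four-participant rule is expressly described in terms of power.
- **The Discussion already urges caution.** It says that a large effect is needed and may not be realistic, and it adds multilevel modelling as more sensitive to smaller effects. This softens the consequence, because the randomization test is one of three analyses. It does not say that power falls short at effect size 1.0 itself, and it goes on to argue that large effects are likely.
- **Ten patients are enrolled.** Pooling would raise power to about 0.78, so 0.48 is not the best figure conceivable for the whole study. But the Power section argues per group of five, no pooled randomization test is described, and 0.78 still falls short of the stated level.
- **A delayed effect can be analysed.** It can, but with the boundary placed exactly right, power is still only 0.44 to 0.53.

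**Conclusion.** The concern holds. For one group of five with start points one week apart, power at effect size 1.0 is about 0.48, against the cited figure above 0.8. It ranges from 0.47 to 0.49 across the plausible lengths of phase B. An effect of about 1.6 would be needed for 0.80. The p < .01 is the minimum attainable p-value, 1/120 = 0.0083, and is obtained in only about one simulated trial in six.

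The 0.48 rests on independent normal errors, an immediate effect in within-phase standard deviation units, and a mean-difference statistic. The article's own expectations make it lower: some autocorrelation takes it to roughly 0.41 to 0.45, and an 8-week delay with an unshifted contrast takes it to about 0.05. Calling the test close to a coin flip is right per group; a pooled test of all ten patients would do better, at about 0.78. The statement needs correcting because it credits the design with a property it lacks.

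**What to change.** Restate the Power section for the design actually used:

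- Per group of five, one-tailed 0.05, effect size 1.0, immediate effect: power about 0.48 without autocorrelation and about 0.42 to 0.44 at an assumed autocorrelation of 0.3.
- Effect size needed for 0.80: about 1.6 without autocorrelation, about 1.7 to 1.75 at autocorrelation 0.3.
- Describe 1/120 = 0.0083 as the smallest p-value attainable with five patients, and present the four-participant rule as the minimum needed for p < .05 to be possible, not as adequate power.
- Give power under the hypothesised 8-week delay for the contrast that will be used: about 0.05 if A versus B is left unshifted, about 0.44 to 0.53 if the boundary is moved by 8 weeks.
- If a pooled test of both age groups is intended, say so and give its figure, about 0.78 under the favourable assumptions.
- State that the literature figure is not specific to a one-week spacing, and point to this section from the caution in the Discussion.

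Allocation, data collection and analysis stay as they are. The cost is rewording, and a stated power that is less favourable.

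### With 120 arrangements per age group, the strict rule p < .05 excludes an attainable p of exactly .05, so the randomization test is valid but runs at 4.17% instead of 5%: a small loss with a free remedy

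*Protocol article*

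**What the plan says.** The Power section of the protocol article says that "the current design of five patients and 33 measurements will be sufficient to reach a statistical significance *p* < .01" and fixes the threshold in the same sentence: "using the Wampold-Worsham procedure [33], with significance reached at *p* < .05".

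The Procedure section defines the randomization. "The following five start points will be randomized: the therapy will start following a baseline period of 5, 6, 7, 8 or 9 weeks". It adds that "each participant will start after a different length of the baseline period", and of the two age groups it says "This approach is similar in both groups".

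Intended statistical analyses makes the test one-sided: "we will use a one-tailed alternative hypothesis, measuring the difference in fatigue severity between phases A and B".

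The planning inputs are also in the Power section: "A series length of 30 has a power over 0.8 when the effect size is 1.0 and no autocorrelation is present". The article does not discuss the discreteness of the p-value or the case p = .05.

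**The concern.** A randomization p-value is a count divided by the number of admissible arrangements, so it takes only a limited set of values. On most grids the nominal .05 falls between two attainable values, and < and ≤ give the same test. Here .05 is itself attainable, so the choice of sign decides whether one arrangement in 120 belongs to the rejection region.

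An exact test that rejects at p ≤ .05 already holds its type I error at 5%. The strict sign therefore gives up part of the rejection region without protecting anything the protocol set out to protect. The Discussion section itself concedes that this test needs a large effect to have adequate power. A result of exactly .05 could also be disputed after the data are seen, and settling the sign beforehand avoids that.

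**Working it through.** **Inputs.** Five patients, Wampold-Worsham procedure, threshold p < .05, effect size 1.0, no autocorrelation (Power). Baselines of 5, 6, 7, 8 or 9 weeks, a different one for each participant, 33 weekly scores, 16 treatment weeks as guideline (Procedure). One-sided A-B difference (Intended statistical analyses). Onset expected about half-way through treatment, mostly after 8 weeks (Background).

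**The plan's own figure.** Five patients over five distinct start points give 5! = 120 arrangements. The smallest p is 1/120 = .0083, which agrees with the statement that p < .01 can be reached. The 120-point grid is thus consistent with the plan.

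**The threshold.** p = k/120, where k is the number of arrangements with a statistic at least as large as the observed one.
- p < .05 requires k ≤ 5, so the size is 5/120 = 4.17%.
- p ≤ .05 requires k ≤ 6, so the size is 6/120 = 5.00%.

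**Power.** This was simulated with full enumeration of the 120 arrangements. The statistic is the sum over patients of mean(A) minus mean(B), with normal errors of SD 1 and a common level shift. The immediate shift and the reading of effect size in units of error SD are assumptions. Phase B was taken either as 16 weeks or as all later weeks. There were 150,000 runs for the immediate 1.0 SD rows, 60,000 for the delayed rows and at least 40,000 elsewhere.

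| Effect | Phase B | p < .05 | p ≤ .05 | Loss (points) |
|---|---|---|---|---|
| 0.5 SD, immediate | 16 weeks | 17.2% | 19.9% | 2.7 |
| 0.5 SD, immediate | all later | 17.7% | 20.3% | 2.6 |
| 1.0 SD, immediate | 16 weeks | 43.5% | 47.6% | 4.1 |
| 1.0 SD, immediate | all later | 44.7% | 48.9% | 4.1 |
| 1.5 SD, immediate | 16 weeks | 72.7% | 76.3% | 3.7 |
| 2.0 SD, immediate | 16 weeks | 91.0% | 93.0% | 2.0 |
| 2.0 SD, immediate | all later | 91.9% | 93.6% | 1.7 |
| 1.0 SD, onset 8 weeks late | 16 weeks | 4.3% | 5.1% | 0.8 |
| 1.0 SD, onset 8 weeks late | all later | 4.0% | 4.7% | 0.8 |

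With no effect, simulated rejection was about 4.0-4.2% and 4.8-5.1%, in line with the exact sizes. At 1.0 SD, first-order autocorrelation of 0.1 to 0.5 leaves a loss of 4.0 to 3.5 points. Scores rounded to whole CIS points give 4.1.

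**Why delay removes the loss.** Take true baseline b, candidate baseline c and delay d ≥ 4 weeks. The earliest onset is then after week 5 + 4 = 9, so no candidate baseline contains a shifted week. A 16-week phase B contains c + 16 − b − d shifted weeks. Summed over the five patients, c is a permutation of b, so the total is 5(16 − d) for every arrangement. The shift cancels, power equals size, and the two rules differ by only about 1/120 = 0.83 points.

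**Other grids.**
- Both groups in one stratified test: 120 × 120 = 14,400 arrangements. The strict size is 719/14,400 = 4.99%.
- Independent draws of start points: 5^5 = 3,125. Since .05 × 3,125 = 156.25 is not a whole number, both rules reject at k ≤ 156, or 4.99%.
- One drop-out kept and a replacement added at the same start point (an assumption): 6!/2! = 360. The strict size is 17/360 = 4.72%, against 18/360 = 5.00%.

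**The case against.** The strongest case on the other side is that nothing here is wrong. The rule p < .05 is the conventional form, a test of size 4.17% is valid, and the phrase closes a sentence in a condensed article. Handling of ties and attainable levels often belongs in a fuller document. That stands as to weight. But the rule is stated here, not left open, and the alternative controls the error equally well.

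Four stronger readings are tempting and are not supported:
- *That about 4 points are lost whatever happens.* This needs an immediate shift near 1.0 SD. Background hypothesises a delayed effect and the Discussion repeats that the therapy needs time. Under that pattern the loss is under 1 point.
- *That p = .05 is a likely result.* It occurs in about 4% of trials at an immediate 1.0 SD effect and about 0.8% with no effect. Nor would it make the trial negative, because visual analysis and multilevel modelling are reported beside the randomization test.
- *That only pooling the two groups removes the issue.* A delayed effect or independently drawn start points does so too.
- *That the remedy cures the power problem.* Power at an immediate 1.0 SD effect is below 50% under either rule.

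The section on refusal and drop-out also allows up to five extra participants per group. The count of 120 is therefore not guaranteed, and a rule written only as 6 of 120 could become wrong.

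**Conclusion.** The point holds as a minor one. For five patients on five distinct start points, tested separately by age group, the stated rule gives a one-sided size of 4.17% where 5.00% is available at no cost in type I error. The article does not say outright that the groups are tested separately. The shared scheme and the sample-size reasoning per group point that way.

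The price depends on the effect: about 4 points of power for an immediate shift of 1.0 SD, roughly 2 to 3 points at 0.5 or 2.0 SD, and under 1 point with an onset at 8 weeks.

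The larger matter in the same section is separate. The cited power of over 0.8 is not reproduced for start points one week apart, where the simulation gives 43-45% under the stated rule.

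**What to change.** Before the data are analysed, restate the rule in the Power section and carry it into Intended statistical analyses: *one-sided p ≤ .05, where p is the proportion of admissible arrangements with a statistic at least as extreme as the observed one, ties counted as extreme (at most 6 of 120 when five patients occupy five distinct start points)*. Defining p as a proportion keeps the rule correct if replacements change the number of arrangements. The bracket then serves only as the worked case.

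The cost is one amended sentence. It needs no patients, measurements or analyses, and the type I error stays at or below 5%. Recruitment was still ongoing according to the Trial status section. The power shortfall needs its own answer.
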